### Study design

This single-center, prospective, randomized controlled test will be conducted in Jingjiang People's Hospital. The sample size was based on the ability to detect a clinically important difference in postoperative quadriceps strength between groups. The protocol was approved by ethics committee of Jingjiang People's Hospital (JJHS-2019-527). Written informed consent will be obtained from each participating patient.

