### Randomization and blind

Once the patients have read and signed the informed consent, those who have met the inclusion criteria will be randomly assigned to one of the two intervention groups: patellar eversion group (n = 50) and patellar retraction group (n = 50).

A computer-generated, permuted-block randomization scheme with a 1:1 ratio between the intervention and control groups will be used, and the software program Stata 14 (Stata Corp LLC, College Station, TX, USA) will be used to carry out the randomization. The allocation will be concealed using sealed and opaque envelopes, numbered consecutively. An independent researcher who will not participate in other study procedures will perform the randomization process. The flow diagram of the study is summarized in Fig. 1.

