### Outcome assessment

Short-term outcomes were as follows: operation time, length of hospital stay, and straight leg raising time. Long-term clinical effect mainly including Insall-Salvati ratio; range of motion at 1 month, 3 months, and 1 year following TKR; and visual analog scale (VAS) at 1 month, 3 months, and Knee Society Score (KSS) score [12, 13] at 1 year following TKR. The ISR Insall-Salvati ratio is the ratio between the length of the patellar tendon and length of the patella. Visual analog scale (0-100 mm): The patients were asked to mark a standardised 100 mm visual analog scale (VAS) ranging from 0 to 100.

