### Data analysis

All statistics were done using SPSS 21.0 (IBM SPSS Statistics for Windows, Version 21.0, Chicago, IL, USA) software. Results for normally distributed continuous variables are expressed as the mean value ± standard deviation, and continuous variables with nonnormal distribution are presented as median values and interquartile range. The statistical analysis was done using a two-tailed Student’s t test. P < 0.05 is considered statistically significant.

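### The secondary functional outcomes are compared by unadjusted t tests; adjusting for a preoperative value, and a repeated-measures model for range of motion and VAS, would be more precise at little cost

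*Protocol article*

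**What the plan says.** Under Outcome assessment, the Protocol article lists four longer-term outcomes, which the Abstract classes as secondary:

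- range of motion (ROM) at three postoperative visits: "range of motion at 1 month, 3 months, and 1 year following TKR";
- pain at two visits: "visual analog scale (VAS) at 1 month, 3 months";
- KSS once, "at 1 year following TKR";
- the Insall-Salvati ratio, which is defined but has no time point.

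No preoperative measurement of any of the four is listed.

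Data analysis names one between-group method for all outcomes: "The statistical analysis was done using a two-tailed Student’s t test". The threshold is "P < 0.05 is considered statistically significant". No covariate, change score or repeated-measures model is mentioned.

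Randomization and blind gives 50 patients per arm, in permuted blocks at 1:1, and names no stratification factor. On the size of the trial, Study design says only: "The sample size was based on the ability to detect a clinically important difference in postoperative quadriceps strength between groups". Quadriceps strength is not among the listed outcomes, so no power is shown for the functional ones.

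**The concern.** A two-sample t test takes no covariate, handles one time point and uses only patients observed at that time. If it is the method for every outcome, three things follow.

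- None of the four comparisons can use a preoperative value, even where that value predicts the postoperative one.
- ROM is tested three times and VAS twice, with no visit marked as the main one.
- A patient seen at 1 and 3 months but absent at 1 year contributes nothing to the 1-year ROM comparison, although the earlier readings carry information about it.

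The Introduction states the goal as comparing short-term and long-term function. ROM, VAS and KSS carry much of that goal, and the trial was not sized for them, so precision that can be had from the same 100 patients is worth taking.

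This concerns the method the article fixes, not detail it leaves out. A fuller plan that adjusted for baseline would have to replace the named test.

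**Working it through.** **Inputs from the article:** 50 per arm, two-sided alpha 0.05, t test. The 50 cannot be reproduced, because no effect size, SD, power or dropout rate is given. The check therefore works back from 50 per arm.

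**Inputs assumed:** the correlation r between preoperative and postoperative values, taken as 0.3, 0.5 and 0.7; a true difference of 0.5 SD to illustrate power; and 10% or 20% of patients missing a visit.

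**Step 1. Detectable difference, unadjusted.** The standard error in SD units is √(2/50) = 0.20.
- Normal approximation, 80% power: (1.960 + 0.842) × 0.20 = 0.56 SD.
- t distribution, 98 degrees of freedom: (1.984 + 0.845) × 0.20 = 0.566 SD, about 0.57.
- Normal approximation, 90% power: 0.65 SD.

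**Step 2. Effect of ANCOVA on the preoperative value.** Residual variance is multiplied by 1 − r². The equivalent unadjusted size is 50/(1 − r²) per arm. The detectable difference is 0.566 × √(1 − r²).

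| r | Variance remaining | Variance cut | Equivalent n per arm | Detectable at 80% (SD) |
|---|---|---|---|---|
| 0 | 1.00 | 0% | 50 | 0.566 |
| 0.3 | 0.91 | 9% | 55 | 0.540 |
| 0.5 | 0.75 | 25% | 67 | 0.490 |
| 0.7 | 0.51 | 49% | 98 | 0.404 |

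With the normal approximation the last column reads 0.560, 0.535, 0.485 and 0.400, so the choice of formula does not matter.

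**Step 3. Power at a true difference of 0.5 SD** (normal approximation). Unadjusted: 0.5/0.20 = 2.50; 2.50 − 1.96 = 0.54; power 70.5%. Adjusted, the ratio becomes 2.50/√(1 − r²), and power is 74.6%, 82.3% and 93.8% for r = 0.3, 0.5 and 0.7.

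**Step 4. Missed visits, t test at one visit.** With 10% missing, 45 remain per arm: 0.5/√(2/45) = 2.37, power 66.0%. With 20% missing, 40 remain: 0.5/√(2/40) = 2.24, power 60.9%.

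**Step 5. Which outcome can gain from which model.**

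| Outcome | Postoperative visits | Baseline adjustment helps | Repeated-measures model helps |
|---|---|---|---|
| ROM | 3 | yes, if recorded | yes |
| VAS | 2 | yes, if recorded | yes |
| KSS | 1 | yes, if recorded | no |
| Insall-Salvati ratio | no time stated | yes, if recorded | no |

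The repeated-measures gain is limited to patients with at least one other postoperative reading, and it rests on data being missing at random.

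**The case against.** The strongest reply is that nothing here is wrong. Under 1:1 randomisation an unadjusted t test is unbiased with complete data, and its standard error already allows for chance imbalance. A journal article may also leave covariates, repeated-measures models and missing data to a fuller plan. Both statements are right. The second does not dispose of the point, because the article does not stay silent on the method: it names one, and a more precise one is available.

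It is also fair to say that the gain presupposes preoperative values the article does not list, and that one range of r is applied to four unlike measures: an angle, a pain score, a composite score and a radiographic ratio. At r = 0.3 the gain is small, from 0.566 to 0.540 SD. This stands, and it is why the size is given as a range.

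A reader might infer more than the documents support:

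- **That the planned comparisons are biased or invalid.** They are not, if data are complete.
- **That the deformity criterion shows a wide baseline spread.** The 20° limit under Participants restricts entry. It says nothing about the spread of preoperative ROM, pain, KSS or patellar height, and no baseline SD is given.
- **That missed visits are a repairable problem for all four outcomes.** KSS has one visit and the Insall-Salvati ratio has no stated time. ANCOVA omits a patient without the outcome just as the t test does.
- **That substantial loss to follow-up is expected.** The article gives no dropout figure; the 10% and 20% above are illustrations.
- **That the trial's main comparisons are affected.** The Abstract makes operation time, hospital stay and straight leg raising time primary, and this point does not touch them.

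**Conclusion.** The point holds as one of efficiency. The named test leaves the preoperative value unused for ROM, VAS, KSS and the Insall-Salvati ratio, and treats each ROM and VAS visit in isolation on available patients. If r lies between 0.3 and 0.7, adjustment is worth between 5 and 48 extra unadjusted patients per arm (55 − 50 and 98 − 50). The exposure to missed visits is real for ROM and VAS only, and its size is unknown. The result rests on the assumed correlation and on preoperative values being obtained. It is a cheap improvement to secondary outcomes, not a defect that makes the planned tests unsound.

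**What to change.** In Outcome assessment, add preoperative ROM, VAS and KSS, and state that the Insall-Salvati ratio is also read from the preoperative radiograph where one is taken. Name the postoperative time point for that ratio, so that its comparison is defined.

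In Data analysis, replace the single t-test sentence for these outcomes with:

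- **KSS and Insall-Salvati ratio:** ANCOVA with treatment and the preoperative value.
- **ROM and VAS:** a mixed model for repeated measures with treatment, visit, treatment-by-visit and the preoperative value. The main contrast is the adjusted difference at the last visit (1 year for ROM, 3 months for VAS), with earlier visits supportive.

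SPSS, the software already named, fits both models. No extra patients or follow-up visits are needed. The cost is a short baseline form if the values are not already collected. Settle this early, because a preoperative value not recorded before surgery cannot be recovered. ANCOVA will not recover patients who miss the single KSS visit.

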### Data analysis

All statistics were done using SPSS 21.0 (IBM SPSS Statistics for Windows, Version 21.0, Chicago, IL, USA) software. Results for normally distributed continuous variables are expressed as the mean value ± standard deviation, and continuous variables with nonnormal distribution are presented as median values and interquartile range. The statistical analysis was done using a two-tailed Student’s t test. P < 0.05 is considered statistically significant.

## Discussion

As a mature surgical technique for the treatment of severe osteoarthritis, TKR can relieve knee joint pain and correct knee joint deformity, improve knee joint function, improve the quality of life of patients, and the clinical effect is promising [14, 15]. In TKR surgery, it is necessary to move the patella to expose the surgical field of view [16]. In conventional TKR, the patella flip is often used to expose the surgical field of view, and the way the patella shifts laterally is more supported by researchers keen on minimally invasive surgery of TKR [17]. Theoretically, the advantage of lateral retraction of the patella is that it can reduce the pressure of the surgical operation on the knee extension device and reduce related soft tissue damage [11]. This procedure is more conducive to the recovery of postoperative extensor function.

The purpose of this randomized controlled trial was to conclude the effect of lateral retraction or eversion on the short-term and long-term functional outcomes of TKR. This study has some highlights. First, this is the first randomized controlled trial about the lateral retraction or eversion for TKR patients for long-term follow-up. In addition, we comprehensively assess the short-term and long-term functional outcomes of TKR. Moreover, we performed rigorous statistical analysis to increase the reliability of our study. Finally, we could provide evidence for clinical guidance.

## Data Availability

All the data pertaining to the present study are willing to share upon reasonable request.

## Abbreviations

TKR: Total knee replacement
BMI: Body mass index
VAS: Visual analog scale
KSS: Knee Society Score
